## Methods/design

### Study design

This is a before-and after study to evaluate the impact and feasibility of upscaling CC screening and treatment services for WLWH attending a rural referral CTC in Tanzania. The main objective is to evaluate the uptake by WLWH attending screening after implementation of HPV testing on a self-sampled cervico-vaginal smear, compared to a retrospective cohort screened by VIA. HPV testing has been implemented in a bundle with: a) a smartphone integrating a mobile colposcope (EVA system, Mobile ODT, Israel) for digital enhancement of VIA examination with cervix magnification and second look/quality control; b) thermal ablation in place of cryotherapy (thus avoiding the need for replenishing nitrogen gas cartridges); and c) LEEP.

We adopted an uncontrolled before-and-after design to compare proportion of WLWH attending screening before and after implementing mentioned interventions. A sub-study with cross-sectional design aims to explore diagnostic performance of two novel tests: the first, QuantiGene-Molecular-Profiling-Histology (QG-MPH), is based on transcriptomic biomarker analysis, while the second is a serological assay to detect antibodies against HPV16-L1 [29], either with a qualitative (Prevo-Check®) or quantitative (PT Monitor®) approach (Table 1. Supplementary material Annex A1 and A2). Further objectives are to determine the adherence to recommendations after screening, to assess the prevalence of HPV genotype-specific infection as well as other co-infections, and to assess feasibility, acceptability and costs of the new implemented screening and treatment plan.

**Table 1 Tab1:** Novel assays

Test	Name	Target	Description
Lateral Flow Assay (LFA)	PT Monitor® (Abviris GmbH, Germany)	HPV16-L1 Ab	Blood-based (serum) competitive immunoassay assessing the presence of epitope-specific antibodies against HPV16-L1. Elevated levels of these antibodies are associated with the presence of HPV16-induced cancer or pre-cancer. A quantitative readout is possible with an optical table-top reader (aLF reader by Qiagen, Germany). CE-marked IVD
Rapid Lateral Flow Assay (rLFA)	Prevo-Check® (Abviris GmbH, Germany)	HPV16-L1 Ab	Qualitative (yes/no) output of LFA (PT Monitor®) in form of rapid capillary point-of-care test with a cut-off of HPV16-L1 Ab > 1000 ng/ml. CE-IVD-marked for the detection of HPV16-induced anal and oropharyngeal cancers
Probe-based RNA Assay	HPV and dysplasia test – QuantiGene-Molecular-Profiling-Histology (QG-MPH)	mRNA of HPV oncogenes and cellular biomarkers	Cell-based. Quantitative detection of HPV16, 18, 26, 31, 33, 35, 39, 45, 51, 52, 53, 56, 58, 59, 66, 68, 73, 82 and cellular biomarkers, correlating with severity of a dysplastic lesion. The emergence and strength of biomarkers define the lesion stage. The QuantiGene 2.0 platform (ThermoFisher) is used 2 Experimental molecular IVD, Charité-University Hospital Berlin, DE (WO2020/161285 A1)

### Setting

The study is conducted in rural south-central Tanzania, at the St. Francis Referral Hospital (SFRH) in Ifakara, a 371-bed designated district referral hospital for the districts of Kilombero and Ulanga (Morogoro Region), serving over 800,000 inhabitants of the valley of Kilombero. Since its accreditation in 2005, a hospital-based HIV Care CTC was built up as a center for integrated care and as a research platform, the "Chronic Disease Clinic of Ifakara” (CDCI), through an international partnership between the hospital, the Ifakara Health Institute (IHI), the Swiss Tropical and Public Health Institute (Swiss TPH) and the University Hospital of Basel, Switzerland (USB) [28]. In addition to participation in the National AIDS Control Program (NACP) cohort, the CDCI has an open, prospective cohort, the Kilombero and Ulanga Antiretroviral Cohort (KIULARCO) [30] since 2008, where approximately 2500 women are currently under active care. At SFRH, CC screening by VIA is performed twice weekly at the Reproductive and Child Health clinic (RCH) and when indicated cryotherapy is offered in a single visit. Further investigations and treatments for VIA + women with major changes or suspicion of CC, including punch biopsy and hysterectomy, are payable services, while screening procedures are for free for WLWH, financed by the MoH and implementing partners of HIV programs and are also accessible at a modest cost (TSZ 500, USD 0,22) for HIV-negative women. For chemo- and/or radiotherapy, patients need to be referred to Ocean Road Cancer Institute (ORCI) in Dar es Salaam. Further opportunities are presented by outreach interventions in peripheral health centers, which are also supported by government implementation partners.

### Eligibility and enrollment

The study recruits consenting WLWH, aged 18 to 65 years, enrolled in KIULARCO, who have been on antiretroviral therapy (ART) for at least three months. Exclusion criteria consist of reported pregnancy, known CC and/or any other condition interfering with the visualization of the cervix, and previous hysterectomy. Participation in the study will be offered as per Standard Operating Procedure (SOP) during routine visits at the CDCI, where WLWH are referred either by the triage nurse or by the attending clinician, or directly at the CC screening service in case of self-referral. Specifically trained nurses will provide, in the native language of Kiswahili, detailed explanations and a copy of the informed consent form (ICF) to eligible WLWH, which will be read aloud to illiterate patients. Any questions or concerns will be answered accordingly. If the patient is willing to participate, the ICF will be signed or marked with their fingerprint and kept in the patient’s data file. Participants will undergo screening and treatment as specified in paragraph “Study procedures”. WLWH not eligible for the study but eligible for screening according to national guidelines, as well as any other women attending screening, will still benefit from digitally enhanced VIA and thermal ablation / LEEP if needed.

### Study procedures

#### Blood sampling

A rapid lateral flow assay (rLFA) (Abviris GmbH, Germany) to detect anti-HPV16-L1 antibodies will be performed first, at the point-of-care (POC), on a single drop of finger capillary blood (as described in Table 2), with qualitative readout. A positive result will address the participant to physical examination / colposcopy at the same visit. Then, a venous blood sample is drawn for a further quantitative read-out serological analysis (Supplementary Materials: Annex A1 und A2).

**Table 2 Tab2:** Procedures

	Screening (day 0)	Baseline (day 0)	Follow-up (Day 1 up to 6 months)	Follow-up (6 months)
Informed consent procedure	X	X		
Eligibility check	X	X		
Case report form (REDCapTM)		X	X	X
Point-of-care blood test (capillary sample) ^a^		X		
Laboratory-based analysis^b^		X		
Cervico-vaginal smear self-sampling ^c^		X		X
Physical examination / colposcopy		X^d^	X	X^d^
Urine		X^d^		X^d^

^a^ PrevoCheck® with qualitative readout

^b^ Serum for PT Monitor® (quantitative analysis) and for Schistosomiasis antibodies

^c^ Seegene Anyplex ™ II 28 HPV, QG-MPH, STI and GS tests

^d^ Only if symptomatic, microscopy for detection of Schistosomiasis eggs

#### Self-sampling procedure

After instruction the participant performs cervico-vaginal self-sampling with the Evalyn® Brush (Rovers Medical Devices B.V., Oss, Netherlands) a medical device designed for this purpose and already validated in large scale screening programs [31, 32].

#### Physical examination / mobile colposcopy

The first participants will undergo physical examination and VIA at baseline visit, in accordance with the national guidelines, as well as HPV-testing as detailed further, until 150 HR-HPV negatives have been examined as a control population for the diagnostic sub-study. Thereafter, only participants that report vaginal symptoms (e.g., vaginal discomfort, abnormal vaginal discharge, pelvic pain, abnormal vaginal bleeding, suspected STI or CC) and/or test positive at rLFA will undergo physical examination at baseline. Otherwise, physical examination is reserved for participants with detected HR-HPV infection, and this will take place at a second visit, due to laboratory turnaround time. Physical examination is performed as per local routine, i.e., with speculum and VIA, in accordance to WHO/IARC standard recommendations [33]. Images are recorded with the aid of a mobile colposcope (EVA system®, MobileODT Ltd, Tel Aviv-Yafo, Israel). Lesion interpretation and classification will be done as specified in Annex A. If the lesion is compatible with an STI or GS, recommendations for treatment will be provided according to National Guidelines [17]. Precancerous lesions will be treated according to severity (Fig. 1 Study Algorithm; Supplementary materials: Annex B).

**Fig. 1 Fig1:**
[figure not shown]
Study algorithm. Cervical cancer screening and treatment pathway at St. Francis Referral Hospital, Ifakara, TZ, before and after implementation of HPV testing. Circled numbers mark at which level could be applied novel tests used in the study. Legenda: Ab: antibody; CIN (1-3): Cervical Intraepithelial neoplasia; HPV: Human Papilloma Virus; ICC: invasive cervical cancer; LEEP: Loop Electrosurgical Excision Procedure; QG-MPH: Quantigene Molecular Profiling Histology; rLFA: rapid Lateral Flow Assay; VIA: Visualisation with acetic acid; WLWH: Woman living with HIV

#### Laboratory analysis

The samples will be stored at room temperature and brought to the IHI laboratory, located next to the SFRH, at the end of the day. Serum will be obtained from the whole blood sample for quantification of antibodies to the HPV16-L1 DRH1 epitope (PT Monitor®, Abviris, Germany). After pre-incubation of 25 µL serum with an HPV16-L1-specific reagent for 5 min, the mixture is transferred onto a lateral flow test cassette. The test result is measured 15 min later with a table-top reader (Qiagen, Germany).

Self-collected cervico-vaginal smear samples are used for HPV testing and QG-MPH, an innovative patented assay by Charité-Universitätsmedizin Berlin (Charité), Berlin, Germany (Charité Technology Transfer, patent WO2020/161285 A1) based on QuantiGene 2.0 (ThermoFisher Inc., Waltham, MA, USA) platform technology. QG-MPH has promising results for detecting CIN3 + with 90% accuracy (i.e., high sensitivity and specificity), and could become a quick onsite-triage method and a pathology-replacing, molecular diagnostic assay [34]. Further details are provided in Annex A2.

The cervico-vaginal swab is fixed in a methanol-based transport medium (ThinPrep® PreservCyt® solution, Hologic N.V., Belgium). HPV testing takes place in two steps: DNA extraction will be performed at IHI Laboratory in Ifakara, where samples undergo temporary storage at -20 °C. Every 1–2 weeks, a batch of 200–400 samples will be transported to the IHI Laboratory in Bagamoyo for PCR-based DNA amplification with the Seegene Anyplex™ II 28 HPV Detection Test (Seegene Inc., Korea), an RT-qPCR assay designed to detect and individually genotype 19 different HR-HPV types (HPV 16, 18, 26, 31, 33, 35, 39, 45, 51, 52, 53, 56, 58, 59, 66, 68, 69, 73 and 82) and 9 low risk (LR)-HPV genotypes (i.e. HPV 6, 11, 40, 42, 43, 44, 54, 61 and 70) in 2 parallel wells. Staff training and laboratory setup for transcriptome analysis in Tanzania was recently hindered by the SARS-CoV-2 pandemic. CFX96™ Dx Real-time PCR System was not lent to the IHI branch of Ifakara because of shortages of the instrument in East Africa. A cervico-vaginal smear sample aliquot will also be shipped for further transcriptome analysis at the HPV laboratory of Charité according to the MTA (Material Transfer Agreement).

Tissue of cervical biopsies and/or LEEP excisions will undergo histopathological studies at ORCI. Urine sediment microscopy for *Schistosoma* egg detection for GS will be performed at the IHI laboratory in Ifakara.

#### Therapy

VIA + women with minor changes are treated at the same session by thermal ablation**,** using a C3 Thermo-coagulator (WISAP Medical Technology, Germany), an easy to handle, reusable, thermo-probe device, which can run on the standard power grid or be connected to an external powerpack, and thus practical in settings where the electricity supply might be interrupted. Similar devices are available at other facilities in the region, the nearest being Morogoro Regional Hospital (ca. 231 km or five hours drive from the study site).

VIA + women with major changes and/or suspicion of ICC and/or transformation zone type 3 are treated at the same visit in a separate session in the gynecology surgical theater by LEEP. LEEP is a 10-min procedure to remove a cone-shaped area of tissue from the cervix for diagnostic and/or therapeutic purposes with a thin wire loop heated by electricity. It has the potential of being curative, usually without significant adverse events [35]. Excised tissue will be sent for histopathological analysis. LEEP surgery is already available at several facilities in Tanzania, the nearest being in Dar es Salaam (ca. 400 km or eight-ten-hours drive from the study site).

#### Follow-up

The follow-up plan is determined by the analysis results (Fig. 1). If antibodies to HPV16-L1 and/or HR-HPV DNA are detected in baseline samples, the participant will be contacted within 7–14 days by phone or, if unreachable, personally notified by a community health worker, in order to plan the physical examination at the patient’s earliest convenience (either at the next CTC appointment or at an extra visit). Independently from these results and any further treatment (LEEP or thermal ablation), participants who have antibodies to HPV16-L1 and/or HR-HPV detected at baseline will be asked to repeat cervico-vaginal swab collection for Anyplex™ II HPV28 Detection and QG-MPH after 6 months. If baseline samples are negative for HR-HPV and for antibodies to HPV16-L1, re-screening will be recommended after 12 months according to the NACP guidelines.

### Endpoints

The primary endpoint is screening coverage, defined as the proportion of WLWH enrolled in KIULARCO screened for CC in the 12 months period after implementation of HPV testing. Participants that undergo screening and transfer out to other CTC within the study period are also included. Secondary endpoints are listed in Table 3.

**Table 3 Tab3:** Endpoints

	Endpoint
**HPV prevalence & persistence**	Proportion of participants with documented HR-HPV, LR-HPV and HPV negative at baseline
	HPV genotypes at baseline
	Proportion of participants with documented HR-HPV, LR-HPV and HPV negative at follow up (6 months after the first sample)
	HPV genotypes at follow up (6 months after the first sample)
	Rate of clearance and persistence of HPV at 6 months follow-up and factors associated with viral persistence
**Cervical lesions**	Prevalence of cervical dysplasia among the patients with HR-HPV
	Prevalence of co-infection (STI and GS)
**QG-MPH® performance**	Prevalence of HSIL/CC detected by QG-MPH® in cervical smear samples
	Diagnostic test accuracy (sensitivity, specificity, PPV, NPV) in detecting patients with CIN3 + compared to colposcopy images, HPV infection detected by Seegene Anyplex ™ II 28 and histology
**Prevo-check® performance**	Prevalence of HPV16 positive CIN2 + detected by Prevo-check®
	Diagnostic test accuracy (sensitivity, specificity, PPV, NPV) in detecting patients with HPV 16 compared to Seegene Anyplex ™ II 28
**PT Monitor® performance**	Comparison of HPV16-antibody levels in women with and without HPV16-positive CIN2 + . Calculation of test performance parameters (sensitivity, specificity, PPV, NPV) at different antibody thresholds and calculation of optimum cut-off for CIN2 + detection by ROC analysis and Youden index
	Diagnostic test accuracies (sensitivity, specificity, PPV, NPV) in detecting patients with HPV16-induced CIN2 + by PT Monitor® compared to colposcopy images, HPV infection detected by Seegene Anyplex ™ II HPV 28 Detection and histology
**Screening strategy implementation**	Acceptability of cervical self-sampling
	Acceptability of proposed implemented pathway
	Adherence to follow-up
	Rate of WLWH completing the CC screening and treatment care plan
	Prevalence of cryo/thermoablation-non-eligible lesions treated with LEEP
	Service accessibility (means of travel to the point of screening: foot, car bajaj, public transport bus; distance to hospital < 5 km, 5—10 km, > 10 km, perceived difficulty of travel yes/no; mean of waiting time in minutes at point of screening)
	Social and educational status of WLWH attending and refusing CC screening as well as their awareness regarding HPV infection, transmission, risk behavior, CC
**Costs**	Direct and indirect costs associated with CC screening and treatment before and after the proposed implementation was adopted including the bundle of interventions
	Direct and indirect costs, as well visit durations, for the current VIA and cryotherapy standard of care and for the implemented path with HPV-based triage

*Abbreviations**: **CC* Cervical cancer, *CIN* Cervical intraepithelial neoplasia, *GS* Female genital schistosomiasis, *HSIL* High Grade Squamous Intraepithelial Lesion, *HPV* Human Papilloma Virus, *HR* High-risk, *LFA* Lateral Flow Assay, *LR* Low risk, *NPV* Negative predictive value, *RNA* Ribonucleic acid, *QGMPH* QuantiGene-Molecular-Profiling-Histology, *STI* Sexual transmitted infection, *PPV* Positive predictive value, VIA Visual Inspection with Acetic Acid, *WLWH* Women living with HIV

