### Statistical analysis

For the primary endpoint, the hypothesis is that implementing a bundle of interventions comprising HPV testing on self-collected samples will improve rates of CC screening among WLWH enrolled in KIULARCO from 8 to 30%. Due to the uncertainty about the WLWH population size, this hypothesis is considered as exploratory, therefore only the precision of the proportion is estimated (screening rate), with a 95% confidence interval. The proportion of WLWH attending CC screening in the post-period will be estimated with 95% confidence interval.

For the secondary and other endpoints no hypothesis will be formulated and results will be compared in an exploratory manner. Diagnostic test accuracies (sensitivity, specificity, positive predictive value and negative predictive value) will be calculated for comparison. Accuracies will be calculated with a 95% confidence interval. Prevalence of secondary endpoints will also be estimated with 95% CI's. Diagnostic tests will be pairwise compared using McNemar test. The assessment of acceptability and feasibility will be evaluated with exploratory statistics. The agreement of raters between diagnostic interpretations will be described with kappa coefficients and polychoric correlations. All secondary parameters will be reported with descriptive statistics including minimum and maximum values, interquartile range, median, mean, SD, count, and proportion as appropriate. Comparisons between study groups will be done using Kruskall-Wallis test for metric or ordinal data and Fisher's exact test for categorical data. A *p*-value < 0.05 (two-sided) is considered as statistically significant.

All evaluations will be done with the latest version of the statistical software R.

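### The primary endpoint says how screened women who transfer out are counted but not unscreened ones; if the latter leave the denominator, coverage is overstated

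*Protocol article*

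**What the plan says.** The Endpoints section of the protocol article gives the primary endpoint as screening coverage, "defined as the proportion of WLWH enrolled in KIULARCO screened for CC in the 12 months period after implementation of HPV testing". The next sentence reads: "Participants that undergo screening and transfer out to other CTC within the study period are also included". Nothing in that section, or elsewhere in the article, says how a woman is counted who transfers out without having been screened.

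Other statements bear on the denominator:

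- **Setting** calls KIULARCO an open cohort and gives its only size figure there: "where approximately 2500 women are currently under active care".
- **Statistical analysis** states the hypothesis that the bundle "will improve rates of CC screening among WLWH enrolled in KIULARCO from 8 to 30" per cent. It then says: "Due to the uncertainty about the WLWH population size, this hypothesis is considered as exploratory". The planned primary result is the post-period proportion with a 95% confidence interval.
- **Sample size** aims at a precision of ±3 points at 30% and ±2 points at 10%, with 1200 women.
- **Eligibility and enrollment** limits participants to consenting women aged 18 to 65, "enrolled in KIULARCO, who have been on antiretroviral therapy (ART) for at least three months", and excludes reported pregnancy, known cervical cancer or other conditions that hinder viewing the cervix, and previous hysterectomy.
- **Discussion** allows that the 8% pre-intervention rate may come from incomplete reporting or mixed data sources. The article gives no transfer rule for that period.

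**The concern.** In an open cohort women enter and leave during the 12 months, so a coverage proportion needs a rule for who stays in the denominator. The only rule given covers leavers who had been screened. The word *also* suggests that leavers would otherwise not count, and having been screened is the stated condition for counting them. If unscreened leavers are not kept as well, membership of the analysis set depends on the outcome, and the estimate can only move upwards.

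The primary analysis is built on precision rather than on a test, so a one-sided error of a few points matters against a ±3-point target. The before-and-after contrast would also be affected if the 8% was counted under a different rule.

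**Working it through.** **Inputs.** From the article: coverage of 30% or 10%, n = 1200, about 2500 women in active care, and the 95% level. Assumed, because the article gives no figure: the share *t* of women who transfer out in the window, and the share *q* of those leavers who were screened first. Let *A* be true coverage among all enrolled women.

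**1. The plan's own precision figure.** The half-width is 1.96 × √(p(1−p)/n).

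- p = 0.30, n = 1200: 1.96 × √(0.21/1200) = 2.59 points, within ±3.
- p = 0.10, n = 1200: 1.96 × √(0.09/1200) = 1.70 points, within ±2.

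The stated precision reproduces. At p = 0.30 and n = 2500 the half-width is 1.80 points.

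**2. Estimate if unscreened leavers drop out.** They make up t(1−q) of the cohort, so

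reported = A / (1 − t(1−q)).

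This exceeds *A* whenever t > 0 and q < 1. If screened leavers enter the numerator while no leaver is in the denominator, reported = A / (1 − t), which is larger still.

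**3. Numbers at A = 30%, q = 30%.**

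| Assumed t | Unscreened leavers dropped | Screened leavers in numerator only |
|---|---|---|
| 5% | 0.30/0.965 = 31.1% | 0.30/0.95 = 31.6% |
| 10% | 0.30/0.93 = 32.3% | 0.30/0.90 = 33.3% |
| 20% | 0.30/0.86 = 34.9% | 0.30/0.80 = 37.5% |

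**4. The same in counts.** Take 2500 women, 250 leavers (75 of them screened) and 750 screened in all.

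- All leavers kept: 750/2500 = 30.0%.
- All leavers dropped: 675/2250 = 30.0%.
- Only screened leavers kept: 750/(2250 + 75) = 32.3%.

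With equal screening rates, either rule that ignores screening status is unbiased. Only the mixed rule is not.

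**5. Other settings at t = 10%.** If leavers are screened half as often (q = 15%, with 30% among those who stay), true coverage is 0.9 × 0.30 + 0.1 × 0.15 = 28.5%, and reported coverage is 0.285/0.915 = 31.1%. At A = q = 10%, it is 0.10/0.91 = 11.0%, an error of +1.0 point.

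**6. When the error passes the half-width h.** With q = A, setting reported − A = h gives t = h / ((A + h)(1 − A)). At A = 30%:

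- n = 2500: 0.0180/(0.3180 × 0.70) ≈ 8%.
- n = 1200: 0.0259/(0.3259 × 0.70) ≈ 11%.

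At 5% transfer the error is 1.1 points, below either half-width.

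**The case against.** The best reply is that the sentence is a harmless clarification. The denominator is defined as women enrolled in KIULARCO. If that means every woman enrolled at any time in the window, unscreened leavers are already in it, and the sentence only confirms that a screening still counts after a move. There is then no bias. The active-care figure stands in the Setting section as a description of the clinic, and nothing makes it the analysis denominator. This stands as a possible reading, but the article does not state it, and it leaves the word *also* with little to do.

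Four stronger readings are tempting and are not supported:

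- **That the protocol includes leavers only if they were screened.** This is the implication of the sentence, not its wording.
- **That the bias exceeds the confidence half-width.** That depends on a transfer rate the article does not give.
- **That the problem exists only in the after period.** The article states no counting rule for the 8%. Silence does not show that a different rule was used, and an article may leave that detail to the full protocol.
- **That the eligibility criteria add to the upward bias.** If only study participants count as screened while all KIULARCO women form the denominator, coverage is pushed down. That premise is itself uncertain: the endpoint speaks of women screened for cervical cancer, and Eligibility and enrollment says that women outside the study can still be screened.

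It is also fair to say that the hypothesis is labelled exploratory and that the Discussion already warns of overestimation. Its warning concerns concurrent influences on uptake, not how leavers are counted.

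**Conclusion.** The point holds as a defect in the primary endpoint definition. A rule is stated for screened leavers and none for unscreened leavers, so on a plain reading inclusion depends on the outcome. A bias follows if unscreened leavers fall out of the denominator, and its direction is then certain: upwards.

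Its size is not known. Under assumed transfer of 5% to 20%, true coverage of 30% and equal screening among leavers, it is about 1 to 5 points, or up to 7.5 points (37.5% against 30%) if screened leavers enter the numerator only. That is comparable with the ±3-point precision target but small beside the hypothesised 22-point rise (30 − 8), which it could not by itself produce.

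**What to change.** Replace the transfer sentence with a denominator set independently of screening. Either of two choices removes the selection:

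- all eligible women in KIULARCO care on the first day of the 12-month window, or
- all eligible women enrolled at any time in the window.

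Keep every such woman whether or not she was screened before transfer, death or loss. Use the same eligibility criteria for numerator and denominator. Apply the same rule to the before window as far as its data allow, and say where they do not.

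The cost is a rewritten sentence and a database query; the linkage to the KIULARCO dataset described under Data collection and management should make this feasible for the after period. Reported coverage may be slightly lower. A start-of-window cohort also leaves out women who enter during the year; a sensitivity analysis that includes new entrants, for example by person-time, would cover them.
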